### Design of the study

2.2.

The INTEGRActiv study is structured in two phases. The first baseline phase (phase 1) is to identify biomarkers of PA and health in a new core cohort of 180 volunteers to be established. In the second phase (phase 2), an educational intervention and its follow-up will be carried out in a subgroup of these subjects (60 volunteers), to allow a first validation step based on the evolution of the identified biomarkers. The general flowchart of the study is illustrated in Figure 1.

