#### Participants

2.3.1.

A total of 180 volunteers (core cohort) will be recruited and distributed into two age groups: prepubertal individuals (*n* = 90), including children, from 8 to 10 years, and postpubertal adolescents (*n* = 90) from 13 to 15 years. Each group will include three subgroups (*n* = 30) of subjects with normal weight (NW), overweight (OW), and obesity (OB) as defined by WHO criteria (38). Volunteers will be equally distributed between both sexes in each group and subgroup. The sample size of the core cohort is based on our previous expertise in different projects aimed at identifying biomarkers (mainly gene expression biomarkers analysed in blood cells by omics techniques), in which we used even a lower number of volunteers [e.g., studies (24, 39)]. Moreover, the combination/integration of different types of biomarkers that will be performed (based not only on gene expression, but also considering lipidomic, metabolic and miRNA profiles) makes its more likely to be able to detect significant metabolic differences and more robust biomarkers. Additionally, the number of volunteers of the core cohort is also expected to be sufficient to achieve the required sample size for the intervention study, which was calculated as explained in Section 2.4.

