### Educational intervention

2.4.

To validate the biomarkers identified in the first stage of the project, an intervention study will be carried out in a subset of the core cohort. All cohort volunteers and their parents will be invited at enrolment to attend a 1 h educational session conducted by two pediatricians at the hospital. Topics covered will include the importance of weight loss in overweight/obesity and its maintenance, a therapeutic nutritional approach to childhood obesity, and the role of PA in cardiovascular fitness. A subgroup of the core cohort encompassing 25% of the participants with normal weight (NW), 25% with overweight (OW), and 50% with obesity (OB), i.e., 60 volunteers (30 for prepubertal and 30 for postpubertal groups) will be formally included in the intervention. Each volunteer participating in the intervention will be given two additional appointments to perform the different proofs/questionnaires and obtain the required biological samples (Table 1). Each individual will be his/her control, so no additional control group is required, and the results will be analyzed individually by performing a pre-post intervention statistical analysis. The number of participants to be included in the educational intervention study has been calculated to achieve a significant 0.2-point BMI *z*-score reduction between the estimated mean and the sampling mean, with a statistical power of 80% and an alpha risk of 0.05 in a one-sided test. This reduction in BMI *z*-score has been associated with a clinically significant improvement in children and adolescents with overweight (62). Potential abandonments will be compensated by incorporating more subjects from the core cohort, which is feasible since educational intervention is offered to all subjects from the core cohort (*n* = 180). A similar sample size has been used with success in previous intervention studies (63, 64).

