#### Integrated analysis

2.6.1.

Data from the PA endpoints (PA, muscular fitness, and CRF describing variables) collected for each individual will be mapped in a principal component analysis plot. Hierarchical cluster analysis will be applied to the PCA scores in order to extract 3 clusters corresponding to low, medium, and high PA scores. The significant differences between the group of individuals will be challenged in a supervised partial-least square discriminant analysis (cross-validation ANOVA and permutation test). All the collected biological data, whether clinical or omics, will be examined in each of the 3 groups of individuals defined therefrom (low, medium, and high PA outcomes). Variables selection to fit the class assignment will be performed independently for each kind of variable with a sight of sparsity. PLS-discriminant analysis (orthogonalized or not), sparse-PLS, and machine-learning methods such as random forest will be applied and resilient variables, selected with all the methods, retained. Statistical models will be built on 4/5 of the population, and their performance assessed by predicting the 1/5 unknowns. This will be iterated 10 times. Complementary AUROC analyses will confirm biomarkers selection robustness. The most resilient variables (expected ∼20 variables from any origin) will be saved, and computed in a final PLS-discriminant analysis. From there, an equation calculated from the beta score of the PLS algorithm and the variable values will be established (using the NIPALS algorithm) to give each individual a score value (with 95% confidence intervals) that fits its PA class (e.g., low, medium, high). This equation will be challenged in the subgroup of the core cohort after the educational intervention. Also, the predictive robustness of the individual score value will be challenged to identified confounding factors (BMI, age, pubertal state, and gender, diet and lifestyle-related factors including sleep behaviour) in a logistic regression model.

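### The final activity equation is challenged only in children who helped build it, so phase 2 cannot validate its classification; variable selection is also not tied to the training splits

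*Protocol article*

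**What the plan says.** The core cohort is the discovery set: "A total of 180 volunteers (core cohort) will be recruited" (2.3.1). Section 2.6.1 forms the outcome from activity, muscular fitness and cardiorespiratory fitness: "Hierarchical cluster analysis will be applied to the PCA scores in order to extract 3 clusters", read as low, medium and high. Several methods then select variables, and those chosen by all of them are kept. Next comes "Statistical models will be built on 4/5 of the population, and their performance assessed by predicting the 1/5 unknowns", repeated ten times. About 20 variables "will be saved, and computed in a final PLS-discriminant analysis", which yields the scoring equation.

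For the test of that equation the section says "This equation will be challenged in the subgroup of the core cohort after the educational intervention". Section 2.4 gives the purpose as "To validate the biomarkers identified in the first stage of the project" and then says where the children come from: "an intervention study will be carried out in a subset of the core cohort". Section 2.2 describes phase 2 as there "to allow a first validation step based on the evolution of the identified biomarkers".

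Section 2.5 adds a screening stage. RNA-Seq and miRNA sequencing are each run in 90 of the 180, the leading genes and up to 20 miRNAs are picked, and these are measured by RT-qPCR in all 180. After the intervention, only candidates that emerged from phase 1 are assayed.

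**The concern.** A test of a prediction rule has to be able to fail when the rule is worthless. Here the phase 2 children supplied part of the data that chose the variables and fitted the coefficients. Chance fit to a child's baseline values carries over to 6 months as far as that child's markers and activity class stay similar. A good phase 2 result could then mean only that children resemble their earlier selves.

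The internal check could have the same weakness. If variables are chosen on all 180 and only the model fit is repeated in each 4/5, the remaining 1/5 has already influenced the choice. Picking genes and miRNAs in 90 children and then assessing them in all 180, screened children included, leaks in the same way.

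At stake is whether the study can say that its score classifies activity level. The Discussion expects robust biomarkers that will guide clinical advice and public policy.

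**Working it through.** **Plan's own figure.** The protocol states no AUROC, accuracy or power for the equation, so there is none to reproduce.

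**Inputs from the protocol**
- Training cohort 180 (2.3.1). Phase 2: 60 of these (2.2, 2.4).
- Split: 180 × 4/5 = 144 for training, 180 − 144 = 36 for testing, ten times (2.6.1).
- Three classes, about 20 variables kept (2.6.1).
- Candidates: around 2,000 miRNAs alone, plus transcriptome, metabolome and lipidome (2.5). Tried: 200, 2,000 and 20,000.
- Sequencing subset 90; for miRNA, 15 × 6 groups = 90 (2.5).

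**Assumptions, not in the protocol.** Equal classes of 60; independent pure-noise variables; the top 20 by ANOVA F stand in for the several selection methods; 2-component NIPALS PLS-DA; correlation ρ between a child's baseline and 6-month marker values. There were 200 runs for 200 and for 2,000 candidates, and 40 for 20,000. Chance is AUROC 0.50 and accuracy 0.33.

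**Step 1: the 4/5–1/5 splits (AUROC for noise)**

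| Candidates | Selection on all 180 first | Screen in 90, then splits on 180 | Selection inside each 4/5 |
|---|---|---|---|
| 200 | 0.73 | 0.64 | 0.50 |
| 2,000 | 0.83 | 0.71 | 0.50 |
| 20,000 | 0.89 | 0.75 | 0.51 |

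With 2,000 candidates, accuracy is 0.66 when selection comes first and 0.32 when it is nested.

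**Step 2: the final equation at 6 months in 60 of its own training children (2,000 candidates)**

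| ρ | Class unchanged | 40% of children move up one class |
|---|---|---|
| 0 | 0.50 | 0.50 |
| 0.3 | 0.63 | 0.59 |
| 0.5 | 0.72 | 0.64 |
| 0.7 | 0.79 | 0.69 |
| 0.9 | 0.86 | 0.73 |

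With ρ = 0.7 and the 60 children kept out of selection and fitting, AUROC is 0.50 to 0.51. In 60 new children it is 0.50.

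A variant with 2,000 features that compares only the low and high classes gives 0.81 to 0.89 for ρ of 0.5 to 0.7 with class unchanged, and 0.63 to 0.71 if activity itself correlates 0.6 over time. It gives 0.50 when those children are left out.

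**Step 3: change instead of class.** With a continuous activity measure, change in a noise score correlates with change in activity at 0.05 to 0.28, depending on ρ and on the stability of activity.

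**Step 4: can the class be rebuilt at 6 months?** The classes use muscular and cardiorespiratory fitness (2.6.1). At 6 months, Table 1 and section 2.4 list accelerometry and questionnaires but neither fitness test. The class as defined cannot be fully re-derived, and falling back on the baseline class is the left-hand column of step 2, the more inflated one.

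**The case against.** Several objections have weight.

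- **Silence on nesting.** The article condenses a fuller plan, and where selection sits relative to the folds is often left to the SAP. A reader might infer from the order of the sentences that selection is done on all 180 before splitting. The text does not say so, and the later saving of the most resilient variables fits selection repeated across the ten iterations. The step 1 inflation is therefore conditional. This does not touch the other half: where the final equation is tested is stated.
- **Refitting.** Fitting the selected variables to all data after cross-validation is ordinary practice. If the whole pipeline was cross-validated, that estimate describes the procedure. This stands, and refitting is not the fault.
- **Role of phase 2.** It is called a first step, based on how the markers evolve, with each child as his or her own control. Those words suit a responsiveness check, for which the same children are needed. But section 2.4 states validation as the aim, and section 2.6.1 challenges a score meant to fit an activity class and names no change-based criterion.
- **Stability is assumed.** A reader might infer that noise is bound to validate in phase 2. The protocol gives no within-child correlation, the intervention aims to change activity, and at ρ = 0 the bias vanishes.
- **Permutation testing.** The permutation test and cross-validation ANOVA are described for differences between the activity groups, not for the selection pipeline. They do not clearly protect against this bias.

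**Conclusion.** The point holds in two parts of different strength.

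The first rests on what the protocol states. The only test described for the final equation uses children who trained it. For assumed within-child stability of 0.5 to 0.7, a noise equation would show a 6-month AUROC of about 0.6 to 0.9, depending on how far activity class persists and whether three classes or only the extremes are compared. Phase 2 therefore cannot serve as validation of the equation's ability to classify activity.

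The second is conditional. If selection precedes the splits, noise reaches 0.83 with 2,000 candidates and 0.89 with 20,000, against 0.50 to 0.51 when nested. Screening in 90 children and then assessing all 180 gives 0.71 to 0.75 for the same two candidate counts. Comparing only low with high can push the split figure to 0.94 (3,000 features), but the plan has three classes, so that figure should not be carried over.

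The documents do not show that the eventual equation will be noise, or that selection is in fact done outside the splits. They show that the stated phase 2 test could not reliably tell a noise equation from a real one.

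**What to change.** 1. **Section 2.6.1, internal performance.** State that every selection step, including the rule of keeping only variables chosen by all methods, is repeated inside each 4/5 training set. Report the 1/5 performance of that whole pipeline as the equation's performance. Genes and miRNAs picked by sequencing cannot be reselected in each fold, because RT-qPCR covers only those already chosen. For these, report performance in the 180 − 90 = 90 children not screened. If the RNA-Seq and miRNA subsets differ, fewer than 90 will be outside both.

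2. **Sections 2.4 and 2.6.1, role of phase 2.** Describe it as a within-child responsiveness check (change in score against change in accelerometer activity), not as validation of class prediction. Read the result against step 3, since noise alone can give a correlation of up to 0.28.

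3. **If a phase 2 AUROC is still reported.** Score each child with an equation whose variables and coefficients were both chosen without that child, limited to markers assayed at 6 months. Cross-fitting the coefficients alone is not enough: that is the selection-first column of step 1, which gives 0.83 before any loss through re-measurement.

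**Cost.** Items 1 and 2 need wording and computing time, with no extra children or assays. The reported AUROC will be lower, the estimate for RT-qPCR markers less precise, and the phase 2 claim narrower. Training only on the other 180 − 60 = 120 children is possible but costs a third of the sample. It also leaves 45/45/30 normal weight/overweight/obesity instead of 60/60/60, because the intervention takes 15/15/30.

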-Glucose, insulin, lipid profile (total, LDL, and HDL-cholesterol; triglycerides), uric acid and creatinine levels will be evaluated in plasma samples of all subjects of the core cohort using standard automated laboratory enzymatic methods. Insulin resistance will be assessed by the homeostatic model assessment (HOMA) index.-Plasma levels of circulating myokines and adipokines of special relevance, such as contraction-induced myokines, myokines involved in muscle-adipose tissue crosstalk, and main regulatory adipokines (Irisin, Interleukin-6 and 15, myostatin, FGF21, leptin, adiponectin, etc.) will be measured using commercial assay kits based on the Luminex® xMAP® technology, and ELISA kits in all subjects of the core cohort.-Whole-genome transcriptomic analysis of PBC samples will be performed by next-generation RNA Sequencing (RNA-Seq) in a representative subset of the core cohort (90 subjects). RT-qPCR analysis of the expression of the most remarkable genes (i.e., those most physiologically plausible and affected) identified in the unbiased transcriptomic study will be used to validate the results in all subjects of the core cohort.-Combined untargeted and targeted metabolomics and lipidomics analysis of plasma will be performed in all subjects of the core cohort by a LIMeX-4D workflow with 4 different liquid chromatography–mass spectrometry (LC-MS) based methods to annotate a wide range of complex lipids, polar metabolites, and exposome compounds (mainly food components and drugs) (65, 66). Promising biomarkers originating from untargeted metabolomics/lipidomics will be quantified using the reference standardization approach (67).-For circulating miRNA analysis, RNA will be extracted from plasma samples using the RNAeasy serum/plasma Kit (Qiagen). A miRNome analysis (around 2000 miRNAs) will be assessed in plasma samples of a representative subset of the core cohort (15 of each of the 6 groups), using miRNA sequencing. The most remarkable miRNAs identified (up to 20) will be analysed in the whole cohort by RT-qPCR.Candidate biomarkers emerging from phase 1 will be measured in plasma and PBC of the subjects in the educational intervention (phase 2) study, at the end of it, using ELISA, RT-qPCR, or biochemical assays, depending on the marker, as above described.

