## Discussion

3.

The INTEGRActiv study will address the scientific and societal challenge of identifying integrated markers reflecting both PA level and health (PA-health biomarkers) in children and adolescents, who represent an important target population to address personalized interventions to improve future metabolic health at a societal level. Implementation of the use of the biomarkers relating PA level and health to be identified in the INTEGRActiv study will help the objective assessment of the actual benefits of public health education interventions and PA programs addressed to children and adolescents that are often developed through schools and the primary health care systems. It can also help identify non-responders requiring special attention so that PA programs more adapted to their characteristics can be recommended. Such public programs are urgently required because unhealthy PA habits among children and adolescents are very prevalent in many countries, going hand-in-hand with a high prevalence of overweight and obesity, and there is the awareness that good physical (and nutritional) habits need to be promoted especially in children and youths for their incorporation into their lifestyle, hence ensuring better adherence throughout life. Furthermore, appropriate levels of PA in these critical stages of development might also be required to ensure a proper biological metabolic programming of long-term health.

All in all, the INTEGRActiv study is expected to encompass relevant progress beyond the state-of-the-art for (a) the definition of potential biomarkers for PA level in childhood and adolescence; (b) the provision of relevant mechanistic information for the link between PA and metabolic health in young subjects; (c) the identification of factors such as age, gender, body weight, sleep behaviour and pubertal status that quantitatively affect biomarker responses; (d) the use and development of new tools in biomarker research, including integrative analysis; (e) further assessment and first-step validation of promising candidate biomarkers in an intervention study. It is expected that newly identified robust biomarkers reflecting PA level and its relation with health (PA-health biomarkers) will guide nutritional/lifestyle and clinical advice and public policies related to endorsing biomarker-based personalised PA, with better adherence and response, to promote health and prevent disease risk factors, starting in the early stages of life.

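### The confounder check in section 2.6.1 appears to test the PLS score against the same PA classes, in the same 180 children, to which the score was fitted, so the adjusted test is strongly anti-conservative

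*Protocol article*

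**What the plan says.** All steps stand in section 2.6.1 (Integrated analysis) of the protocol article, in this order.

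1. A principal component and cluster analysis of the PA, muscular fitness and cardiorespiratory fitness data is used to "extract 3 clusters corresponding to low, medium, and high PA scores".
2. The biological variables are then screened against these classes: "Variables selection to fit the class assignment will be performed independently for each kind of variable". Models are built on 4/5 of the children and checked on the other 1/5, ten times.
3. "The most resilient variables (expected ∼20 variables from any origin) will be saved, and computed in a final PLS-discriminant analysis".
4. The equation from that final model serves "to give each individual a score value (with 95% confidence intervals) that fits its PA class (e.g., low, medium, high").
5. The equation is challenged after the intervention in a subgroup of the same cohort.
6. In addition, "the predictive robustness of the individual score value will be challenged to identified confounding factors (BMI, age, pubertal state, and gender, diet" and lifestyle factors including sleep, in a logistic regression.

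No hold-out is stated for the final equation or for the scores in step 6, and the dependent variable in step 6 is not named. Section 2.6 sets the significance threshold at P < 0.05. On cohort size, section 2.3.1 says: "A total of 180 volunteers (core cohort) will be recruited".

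**The concern.** An ordinary adjusted logistic test takes the covariate as given, built without sight of the outcome. Here the score is built from the outcome. The class labels decide which variables are kept and then set the PLS weights. Part of what the weights pick up is chance agreement with the class that the confounders do not explain. When the same labels become the logistic outcome, that agreement counts as evidence that the score adds to BMI, age, pubertal state, sex, diet and sleep.

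This is the only analysis in the article that tests the score itself against the confounders. Age and weight are built into the design as six cells, so markers that track them are easy to find. The Discussion also promises "the identification of factors such as age, gender, body weight, sleep behaviour and pubertal status that quantitatively affect biomarker responses" and markers fit to guide clinical advice and public policy. If the test passes mainly because of the fitting, a score that reflects body size and age could be reported as an independent marker of PA.

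**Working it through.** The article gives no figure for this check, so there is none to reproduce. The size was found by simulation under the null that the markers carry nothing about PA beyond the confounders.

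**From the article:** 180 children in 2 age groups × 3 weight groups, balanced by sex; 3 PA classes; about 20 variables in the score; threshold 0.05. On the number of candidates, section 2.5 says "A miRNome analysis (around 2000 miRNAs) will be assessed" (in a subset), with transcripts, metabolites and lipids besides.

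**Assumed:** 100 to 3000 candidates, all measured in all children; PA cut at tertiles; outcome high class versus the rest; two-sided test; confounding strength over a wide range, because the article gives none.

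**Model.** PA = g(−b + 0.5a + 0.5s) + e, where a and s are ±1 for age group and sex, b is weight group (−1, 0, 1) plus noise of SD 0.3, and e has variance 1. The explained variance is g²(2/3 + 0.09 + 0.25 + 0.25) = 1.257g², so R² = 1.257g²/(1.257g² + 1). For g = 0.25, 0.5, 0.75, 1, 1.5 and 2, R² is 0.07, 0.24, 0.41, 0.56, 0.74 and 0.83. A share of the markers loads on a, b and s with loadings of SD up to 1.5; the rest of each marker is independent noise.

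**Score.** Twenty markers with the largest class F statistics (in most runs, stable over ten random 4/5 splits), or 20 fixed beforehand; then a two-component PLS fitted to class.

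**Test.** LR = 2(l₁ − l₀) on 1 df, where l₀ has age, BMI and sex and l₁ adds the score. The table gives the share of trials with P < 0.05 (60 to 600 trials per row).

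| Variables | Share of markers tied to confounders; loading SD | R² | Same children (as planned) | Out-of-fold score, two-sided | New children |
|---|---|---|---|---|---|
| 20 of 1000 | 20%; 0.3 | 0.07 | 100% | 14.0% | 4.7% |
| 20 of 2000 | 30%; 0.5 | 0.24 | 100% | 18.3% | 3.3% |
| 20 of 3000 | 5%; 1.0 | 0.24 | 92.5% | 18.8% | 1.3% |
| 20 of 300 | 20%; 0.5 | 0.41 | 90.0% | 14.7% | 6.0% |
| 20 of 1000 | 5%; 1.0 | 0.56 | 42.0% | 14.0% | 7.3% |
| 20 of 2000 | 100%; 1.5 | 0.74 | 95.0% | 14.0% | 8.0% |
| 20 fixed | none | 0.24 | 95.3% | 14.8% | 4.5% |
| 20 fixed | 100%; 0.5 | 0.24 | 62.7% | 14.0% | 5.7% |
| 20 fixed | 100%; 1.0 | 0.56 | 13.7% | 10.8% | 4.7% |

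Over all settings with selection, the planned analysis rejects in 90–100% of trials for R² of 0.07 to 0.41 and in 42–95% for R² of 0.56 to 0.83. With 20 fixed variables the range is 14–98%; the upper end comes from further runs with none or 20% of the markers related to age and BMI. The same equation in new children rejects in about 1–10%, which is the nominal 5% plus simulation noise. The inflation therefore comes from reusing the labels.

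**What out-of-fold scores achieve.** Two-sided, one 5-fold partition gives 7.5–25%, and scores averaged over ten iterations 13.5–27.5%. If only positive (PA-predictive) coefficients count, the single partition gives 0.4–4.5% against a nominal 2.5%, and up to 7% in a further set of 300-trial runs. Most of the excess thus lies in the negative direction, and a plain two-sided comparison is not calibrated.

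**Coverage of the splits.** If the ten 4/5–1/5 splits are independent, a child is never held out with probability 0.8¹⁰ = 0.107, which is about 19 of 180 children without an out-of-fold score.

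**The case against.** The strongest objection is that the article gives this model one sentence, with no outcome, no statement of which scores enter and no decision rule. That stands as a limit: PA class and all-cohort scores are inferred. But the score is built to predict PA class, no other target for its predictive robustness is evident, and the only scores described come from the final equation. The problem is the stated sequence, which a fuller plan following it would inherit.

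A second objection points to other safeguards. The 1/5 hold-out would expose markers that are pure noise. It would not expose markers that predict PA only through age or BMI, and that is the case the confounder check exists for. The splits also precede the final equation and together use every child's label. The post-intervention challenge reuses the same children. The ANCOVA in section 2.6 is a general option, not a test of the score.

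Third, a reader might infer that the check can never fail, or that fitting the weights alone always breaks it. The simulations do not support this. The rate falls to 42% with selection and to 14% with fixed variables when confounders explain more than half of PA.

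Fourth, this is one supporting check in a discovery phase, with no sample size tied to it. That is true, and it limits the consequence to what may be claimed for the score.

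**Conclusion.** The concern holds on the natural reading of section 2.6.1. With selection, as planned, a score with no PA information beyond the confounders passes the check in about 90–100% of trials under weak to moderate confounding and 42–95% under very strong confounding, against a nominal 5%. A significant adjusted score would therefore not show that it is more than a proxy for age, sex and BMI. This does not mean that the score is a proxy; the planned test simply cannot tell.

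The figures rest on PA class being the outcome, on all-cohort scores being entered, on the assumed confounding strengths, and on an F-statistic screen standing in for the planned consensus of PLS-DA, sparse PLS and random forest. Diet, sleep and pubertal state were not simulated separately. Nor do the documents support the inference that out-of-fold scores with an ordinary likelihood-ratio test would restore 5%; the simulations contradict it.

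**What to change.** In section 2.6.1:

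- Name PA class as the outcome of the confounder model, and say how its three levels are handled.
- Enter out-of-fold scores only: each child's score comes from an equation whose variable selection and PLS weights were both obtained without that child.
- Use 10 repeats of a 5-fold partition, so that every child is held out once in each repeat.
- Compare the confounders-only model with the model that adds the score. Use a directional test, in which only a positive, PA-predictive coefficient counts, or a permutation test that preserves the relation between class and confounders and reruns selection and fitting each time. Do not use a plain two-sided likelihood-ratio test. The permutation test is the safer choice, because the directional rates above scatter around nominal and come from single 5-fold partitions.
- Report the gain in out-of-fold AUROC over the confounders alone.
- Do not use scores from the final all-cohort equation for this test.

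One limit should be stated with the result. Transcripts and miRNAs are shortlisted in a sequenced subset before measurement in the whole cohort. Where that shortlist uses PA class, it cannot be redone within folds.

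The cost is a few sentences and more computing, with no new data. The equations are fitted on 4/5 × 180 = 144 children, so the adjusted effect will look somewhat smaller.
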